## Abstract

**Background:**

The majority of children referred to Child and Adolescent Mental Health Services (CAMHS) in the UK will present with mixed emotional and behavioural difficulties, but most mental health treatments are developed for single disorders. There is a need for research on treatments that are helpful for these mixed difficulties, especially for school-age children. Emotion Regulation (ER) difficulties present across a wide range of mental health disorders and mentalizing may help with regulation. The ability to mentalize one’s own experiences and those of others plays a key role in coping with stress, regulation of emotions, and the formation of stable relationships. Mentalization Based Therapy (MBT) is a well-evidenced therapy that aims to promote mentalization, which in turn increases ER capacities, leading to decreased emotional and behavioural difficulties. The aim of this study is to test the clinical- and cost-effectiveness of MBT compared to treatment as usual for school age children with emotional and behavioural difficulties. If effective, we hope this approach can become available to the growing number of children presenting to mental health services with a mix of emotional and behavioural difficulties.

**Materials and methods:**

Children referred to CAMHS aged 6–12 with mixed mental health problems (emotional and behavioural) as primary problem can take part with their parent/carers. Children will be randomly allocated to receive either MBT or treatment as usual (TAU) within the CAMHS clinic they have been referred to. MBT will be 6–8 sessions offered fortnightly and can flexibly include different family members. TAU is likely to include CBT, parenting groups, and/or children’s social skills groups. Parent/carers and children will be asked to complete outcome assessments (questionnaires and tasks) online at the start of treatment, mid treatment (8 weeks), end of treatment (16 weeks) and at follow up (40 weeks).

**Trial registration:**

**Clinical trial registration:**
ISRCTN 11620914.

## Introduction

In 2021, one in six (16.0%) children in England aged 5 to 16 were identified as having a probable mental disorder [1]. The majority of these children, when presenting to child mental health services, do not receive an evidence-based treatment. This is partly because most empirically tested treatments were developed to treat single disorders [2, 3], whereas the evidence indicates that the structure of mental health symptoms does not straightforwardly map onto traditional diagnostic categories and comorbidity of mental health problems is high [4, 5]. Indeed, most children referred for treatment show high rates of transdiagnostic co-morbidity–this is the rule, not the exception [6]. As a result, there is a significant research-practice gap.

A solution to this research-practice gap is for clinical trials to focus on transdiagnostic interventions that target causal and maintaining factors underlying a range of clinical presentations. Transdiagnostic interventions are especially suitable for children, who show a great overlap in symptoms and a high level of transitory symptoms across developmental stages [7–9]. Transdiagnostic interventions also have good potential for implementation, as they allow clinicians to address diverse diagnoses and sub-threshold symptoms within a single treatment model, and simultaneously target multiple problem areas, so limiting training burden on clinicians [9–11].

Because of the ubiquity of emotion regulation (ER) difficulties across a wide range of psychopathologies, research has identified ER as a core transdiagnostic mechanism [12]. ER refers to implicit and explicit processes and strategies involved in regulating emotional states. Both adequate down-regulation of negative emotional states and up-regulation of positive states during childhood play a critical role in adaptive development and well-being [13]. ER difficulties have been associated with risk of psychopathology across both emotional and behavioural disorders [14–16]. Findings of a recent meta-analysis suggest that interventions can enhance ER in youth, and that these changes correlate with improvements in psychopathology [17]. However, of the 21 studies in the meta-analysis, only 4 targeted children aged 6–12, thereby highlighting a significant evidence gap for this age group. In addition, most research and interventions have neglected the role of positive/adaptive ER strategies, despite recent research highlighting their importance, especially for children and young people [17].

The capacity to ‘mentalize’ is now recognised as a key component of positive or adaptive ER [18]. Mentalizing has been defined as ‘the process by which we make sense of each other and ourselves, implicitly and explicitly, in terms of subjective states and mental processes’ [19] (p. 11). The ability to mentalize one’s own experiences and those of others plays a key role in coping with stress, regulation of emotions, and the formation of stable relationships [18]. Empirical studies have shown that deficits in the capacity to mentalize are predictive of maladaptive ER in both clinical and non-clinical populations [20, 21], and that there are deficits in mentalizing capacity among children with either internalizing or externalizing psychopathology [22–25].

The importance of parental mentalizing to the well-being of children is also clearly established. Parental mentalizing has been found to be significantly associated with both child’s internalizing and externalizing symptoms and social–emotional competencies [26]. The quality of a carer’s mentalizing is positively associated with sensitive caregiving, strengthened parent-child relationships, and secure attachment [27, 28]. Parents with higher mentalizing capacity are better able to tolerate emotional distress in their children, which is thought to be helpful in managing parenting stress [29]. A systematic review exploring the association between parental mentalizing and children’s mental health outcomes [30] highlighted that poor maternal mentalization is associated with overcontrolling parenting [31], a higher incidence of child anxiety [32], child emotion regulation difficulties [33] and greater child externalizing behaviours [34].

Mentalization Based Treatment (MBT) was originally developed as a treatment for adults with a diagnosis of borderline personality disorder [19], where emotion dysregulation is a key feature. The evidence base for its effectiveness with this group is good [35]. More recently it has been adapted for therapeutic work with children and families [36]. For school age children, there is preliminary evidence that promoting a child’s mentalizing capacity can improve ER and symptomatic improvement, including children’s behavioural and emotional difficulties [24, 37]. Moreover, improvement in parents’ capacity for mentalizing has been associated with reductions in children’s internalizing and externalizing problems [38]. However, as a recent systematic review has highlighted, high quality clinical trials of MBT for school-age children are lacking [39], and time-limited MBT has yet to be evaluated as a transdiagnostic intervention for school-age children.

In summary, given that many children presenting to mental health services experience comorbid difficulties, there is a need for evidence-based transdiagnostic interventions that effectively target mechanisms underlying co-occurring mental health difficulties; ER is the best-evidenced mechanism implicated in a range of common mental health disorders. MBT is a well-evidenced therapy for a range of populations that aims to promote mentalization, which in turn increases ER capacities, leading to decreased emotional and behavioural difficulties. Until now, children under 12 have not had the benefit of this transdiagnostic approach, as the evidence for its effectiveness in this population has not yet been examined. The aim of this study is to test the clinical- and cost-effectiveness of MBT against treatment as usual (TAU) for school-age children with comorbid internalizing and externalizing difficulties. We will conduct the first randomised controlled trial of MBT for this population and examine the role of ER as a mediator of treatment response. Our hypotheses are as follows:

Hypothesis 1: Children allocated to MBT will experience a significantly greater reduction in mental health problems–both internalizing and externalizing–when compared with the TAU group.Hypothesis 2: Families allocated to MBT will also experience a greater improvement in a range of secondary outcomes, including improved capacity for emotion regulation, and decreased parental stress, and a reduction in health and social service use and costs compared to the TAU group.Hypothesis 3: The impact of treatment on child mental health will be mediated, in part, by changes in capacity for emotion regulation (in both parent and child).

The Implementation and Process Evaluation (IPE) aims to investigate: a) model fidelity, b) the experience of MBT (including the change process) from the perspective of service users; and c) any barriers to implementation and scalability post-trial.

If effective, we hope this scalable, transdiagnostic approach can become available to the growing number of children presenting to mental health services with a mix of internalizing and externalizing difficulties. In addition, it may enable a more efficient allocation of health and social care resources by reducing the need for longer-term, more intensive specialist mental health interventions.

## Materials and methods

### Trial design

This study will be a pragmatic, individually randomized, superiority trial comparing MBT with TAU, with those administering outcome measures and analysing the data, blind to group assignment. An internal pilot will inform the optimal delivery of the main study, which will be a fully powered, randomised control trial of the intervention. Both the internal pilot and main trial will have an embedded qualitative component. Assessments of capacity for ER will enable mediator analyses to identify mechanisms underlying symptom change.

The internal pilot will take place before the main RCT, across two NHS Trusts, following the same recruitment and data collection procedures as the main trial. The internal pilot will be an opportunity to test a) the process and procedures of training and supervising the practitioners delivering MBT; b) the recruitment processes (including screening of referrals and contact with families); and c) the feasibility of data collection processes. With regard to this third aim, this will include feasibility of remotely conducting two task-based assessments of emotion regulation. Recent recommendations for the assessment of emotion regulation processes suggest that researchers adopt a multi-modal approach, where self-report measures are complemented with task-based and/or observational measures, although few studies have done this sufficiently especially as part of clinical trials [17]. Hence, one of our objectives for the internal pilot phase is to explore the feasibility of our multi-modal assessment approach as part of a clinical trial and test the convergence validity of the different ER measures. If successful, we will carry forward self-report and one or both task-based ER measures to the main trial where they may be employed at baseline only.

### Study setting

The study will be set in two large mental health trusts in the UK: Barnet, Enfield and Haringey (BEH) Mental Health NHS Trust and Oxford Health NHS Trust, which between them run 12 child and adolescent mental health services (CAMHS). Involvement with the study is supported at senior management level within these CAMHS. These services receive over 3,000 referrals of children aged 6–12 per year, from a diverse cultural and social background. The services are multi-disciplinary, including clinical psychologists, child psychiatrists, child psychotherapists, family therapists, social workers, primary mental health workers and clinical nurses.

### Participants

320 children aged 6–12 with mixed (internalizing and externalizing) mental health problems, and their parents/carers. Children will be recruited from referrals to participating CAMH services.

Based on data available from services, approximately 60% of referrals are accepted as suitable for CAMHS, and a case file review has indicated that approximately 40% of accepted cases are likely to meet our inclusion criteria, with the majority of other referrals in this age group related to Autistic Spectrum Disorder (ASD) or neurodevelopmental disorders. This would make an estimated eligible pool of 720 children per year. We anticipate a consent rate of approximately 40–50%. The number of children included in each participating CAMHS team will be monitored by the trial team throughout the recruitment phase of the study. If the intake of children falls behind recruitment targets, appropriate action will be taken, including the possibility of adding additional clinical sites to the study.

During the internal pilot we will aim to recruit 40 families to the study (20 to MBT, 20 to Treatment as Usual). The research team will monitor recruitment during the pilot phase in order to identify any barriers to recruitment and to allow for any changes in procedure.

### Eligibility criteria

#### Inclusion criteria

Child aged 6–12; carer-reported Strengths and Difficulties Questionnaire (SDQ) total difficulties score for child of ≥14 with emotional problems ≥5 and conduct score ≥3; combined with a functional impairment score of ≥1.

#### Exclusion criteria

Current participation in another mental health intervention trial. A pre-existing clinical diagnosis (in child or parent) of: psychotic disorder, ASD, pervasive developmental disorder, eating disorder, severe learning difficulty, or (in parent) severe substance abuse disorder. Children will also be excluded where the referring clinician identifies an immediate risk of harm to self or others.

### Recruitment, screening and gaining informed consent

The study began recruitment in April 2023 and will recruit participants over a 16-month period (4 months for the internal pilot, and 12 months for the main trial), with the pilot sites continuing to recruit while data from the internal pilot is analysed and sites are set up for the main trial. A SPIRIT schedule of enrolment, interventions, and assessments is presented in Fig 1, and participants’ journey through the trial is mapped out in Fig 2, and specific aspects are explained in more detail below.

**Fig 1 pone.0289503.g001:**
[figure not shown]
SPIRIT schedule of enrolment, interventions, and assessments.

**Fig 2 pone.0289503.g002:**
[figure not shown]
CONSORT diagram.

All new referrals will be initially screened by a member of the CAMHS intake team to see if the child will be aged 6–12 by the time of randomisation and that there are no indications that any exclusion criteria apply. The parents/carers of those children who may be eligible will be offered further information about the study; consent will be sought from the family to pass the parent’s contact details to the research team. The research team will then send information sheets by email to those parents/carers who have agreed to share their contact details, along with a link to a screening questionnaire. If the screening questionnaire indicates that the child is eligible, the research team will offer a telephone/video call to discuss the study further and answer any questions the parent/carer may have. If the family is interested in the study, the parent/carer will be sent a link to the eConsent form. Children will be invited to provide eAssent to participate at study entry, and verbal assent will be sought by researchers prior to commencing optional interviews and tasks.

Once informed consent has been granted, the parent/carer will be able to access and complete the parent/carer and child baseline questionnaires online. At the family’s request, all measures can also be completed on a call with the research team while accessing a blank PDF version of the questionnaires. A video call with the family will be arranged for completion of the Test of Emotional Comprehension (TEC) task and parent-child interaction task, if agreed to in eConsent form.

### Randomization

Once mandatory elements of baseline data collection have been completed, participants will be randomized to either MBT or TAU, stratified by CAMH service and age group (6–9 years and 10–12 years old), using permuted blocks of size 2 within each stratum. The randomization sequence will be generated from random numbers generated in the R software for statistical computing [40] and pre-loaded into the REDCap data management platform, which will be used for data collection.

The randomization sequence will be stored but concealed within the REDCap data capture system. When all information relevant for stratification (CAMH service and age) has been completed, a researcher has the option to initialize randomization. Only then will the allocation be revealed within the REDCap database, and the CAMH service will be informed of the result of the randomization, so that treatment can be initiated.

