### Statistical plan and data analysis for main trial

#### Sample size and power calculation

The total sample size for the study will be 320. The power analysis was informed by an analysis of 71,763 UK CAMHS clinical records held by the Child Outcomes Research Consortium (CORC, https://www.corc.uk.net/), as well as by published psychotherapy trials in CAMHS settings. CORC data suggests that children meeting our inclusion criteria have a mean SDQ Total Difficulties score of 24.6 at presentation to CAMHS, with a standard deviation of 5.0. This score is our primary outcome. We assumed that the smallest clinically meaningful post-treatment difference on the SDQ is 1.5 points, which is equivalent to a standardised treatment effect difference of 0.3. The power analysis aimed to establish the number of children per therapist to give at least 80% power to detect this effect at the 5% significance level using a two-sided test. The statistical model will account for clustering of children within therapists, and of therapists within the CAMHS, via random intercepts. We will adjust for baseline SDQ scores.

We calculated the required sample size based on published formulae [59] and made the following assumptions: The within-patient correlation was assumed to be within-patient = 0.6, which is close to the median value of 0.59 estimated by a meta-analysis of within-patient correlations [60]. We estimated that 40 therapists will participate in the study and assumed a therapist effect of ICC therapist = 0.02. We think this ICC is conservative. There is little data on therapist ICCs in CAMHS settings specifically, but the recent Improving Mood with Psychoanalytic and Cognitive Therapies (IMPACT) trial, set in English CAMHS, reported ICC < 0.01 [61]. A smaller therapist ICC would increase power. The power analysis assumed that outcomes do not vary by CAMHS, which is also conservative. If there was intra-site correlation, power would increase, since each service would act as its own control. Given these assumptions, and allowing for 15% loss to follow-up, the total required sample size is *N* = 320 (160 children per treatment group, 8 children per therapist). The calculated power under this design is 80.8%.

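### Fixed, published blocks of size 2 make the second allocation of each complete pair (up to 160 of 320) deducible by anyone who knows the previous result in that stratum

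*Protocol article*

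**What the plan says.** The Randomization section allocates children 1:1 to MBT or TAU within strata formed by CAMH service and two age groups (6–9 and 10–12), "using permuted blocks of size 2 within each stratum". One fixed size is given, with no mention of varying it. The list is protected: "The randomization sequence will be stored but concealed within the REDCap data capture system". An allocation is revealed only when randomisation is triggered, after mandatory baseline data are in. At that point "the CAMH service will be informed of the result of the randomization, so that treatment can be initiated".

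Under Recruitment, screening and gaining informed consent, in the text after Fig 2, "All new referrals will be initially screened by a member of the CAMHS intake team". The Blinding section says that Trial Managers start randomisation, that the result goes straight to site staff, that families are not blind, and that research assistants and analysts are.

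On size, "The total sample size for the study will be 320", with "160 children per treatment group, 8 children per therapist". Study setting counts 12 services across the two trusts.

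**The concern.** Two is the smallest possible block and the most predictable. Hiding the list in REDCap stops anyone reading it. It does not stop someone deducing the next entry from the previous result and the published block size. Each stratum lies inside one service, and that service receives all of its own results, so the information needed for the deduction collects where referrals are first screened.

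Recruitment is slow enough for this to matter. With 320 children over 16 months and up to 24 strata, a stratum receives 320 / (16 × 24) = about 0.8 children a month. A known next allocation can stand open for weeks.

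The risk is selection bias. If children with a better outlook are more likely to fill slots known to be MBT, or the reverse, the arms differ before treatment starts. The analysis can correct only for what was measured.

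**Working it through.** **The plan's own figures.** The article gives no predictability figure to reproduce. Its 80.8% power is recovered to within 2 points: 160 × 0.85 = 136 analysed per arm, difference 1.5, SD 5.0, variance factor (1 − 0.6²) × (1 + 7 × 0.02) = 0.64 × 1.14 = 0.73. This gives 82.5% with a normal reference and 80.6% with a t reference on 38 df. The present point leaves that figure unchanged.

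**Predictability of fixed blocks.** For each block size, all 1:1 sequences were enumerated. Counted were the positions fixed with certainty by earlier ones, and the success rate of always guessing the arm with more places left.

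| Fixed block size | Certain share | Out of 320 | Best-guess success |
|---|---|---|---|
| 2 | 50% | 160 | 75% |
| 4 | 33.3% | 107 | 70.8% |
| 6 | 25% | 80 | 68.3% |

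For size 2 this can be done by hand. The first slot is a coin toss (0.5) and the second is certain (1), so the average is (0.5 + 1) / 2 = 0.75.

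**Incomplete pairs.** Assume all 12 services take part and the 24 strata are equally likely. About half of the strata then end on an odd count, leaving about 12 unpaired children, so (320 − 12) / 2 = 154 allocations are certain (48%). Simulation agrees: mean 154, range 150 to 159.

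**Varying block sizes.** The mean stratum size is 320 / 24 = 13.3, taken as 13.
- Fixed size 2: 6 of 13 slots are certain (46%), and the best-guess rate is (6 + 7 × 0.5) / 13 = 73%.
- Sizes 2, 4 and 6 mixed with equal probability, against an observer who knows the possible sizes but not their order (simulated): about 3% of slots are certain, and the best-guess rate is 68%.

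**What steering could do (illustration; the inputs are assumptions).** Half of the slots are predictable. Let a fraction f of them be steered, and let children steered to one arm differ in prognosis from those steered to the other by 2 SDQ points *after* baseline SDQ adjustment. Bias = 0.5 × f × 2.
- f = 0.2: 0.2 points, or 0.2 / 1.5 = 13% of the target difference.
- f = 0.5: 0.5 points, or 0.5 / 1.5 = 33%.

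**The case against.** A reader might infer that allocation concealment fails for half of the children. The article does not support that. The stored sequence stays hidden until randomisation is triggered, and prediction needs someone who follows the order of results within a stratum. The article says that the service, or its staff, receives results. It does not say that the person screening referrals does. That Trial Managers remember past results is likewise an inference.

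Several steps also stand between intake and a slot. The family agrees to share contact details, completes a screening questionnaire, speaks to the research team, consents and finishes baseline. Expected consent is only 40–50%. An intake worker can seldom tell whether a given child will land in a first or second position. Eligibility rests mainly on carer-reported SDQ and impairment cut-offs, so the idea that staff could bend eligibility at large goes too far. Their discretion lies in the exclusion flags and clinician-identified immediate risk.

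The primary model adjusts for baseline SDQ, so steering on visible severity would be partly removed. It is also tempting to say that assessor blinding is broken because one child's arm reveals the partner's. That requires a research assistant to know both the arm and the pairing, and nothing says they do. The primary outcome is a parent-rated questionnaire in any case.

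All of this narrows the concern. What stands is that intake acts before consent, that whoever starts randomisation can affect timing or order, and that unmeasured prognosis, such as family engagement, is not adjusted away.

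**Conclusion.** The point holds as a weakness of design, with no evidence of actual bias. Up to 160 of 320 allocations (about 154 under equal strata) can be deduced by anyone who knows the block size and the previous result in the stratum. The block size is public, and the services that screen referrals are told the results.

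The shares follow exactly from the stated block size. The figures per stratum rest on 24 equal strata. The 0.2–0.5 point bias rests on an assumed steering rate and on an assumed 2-point difference that survives baseline adjustment, and should not be quoted without those conditions. This should be fixed, and it is a cheap improvement.

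**What to change.** If recruitment is still open, load a new REDCap allocation table for all unused positions, keeping the same service by age-group strata but with randomly varying block sizes (for example 2, 4 and 6). A statistician not involved in enrolment should generate it. The new sizes should be withheld from Trial Managers, researchers and sites, and left unpublished until recruitment ends. The published size of 2 cannot be withdrawn, so the gain applies only to children not yet randomised.

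For children already randomised, compare baseline SDQ between first and second positions of a pair, by arm. This check is coarse. Even with 80 second-position children per arm, the standard error of the difference between arms is 5 × √(2/80) = 0.79, a 95% interval of about ±1.5 points. A clean result would be reassuring but would not exclude modest steering, nor steering on unmeasured features.

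Cost: a new table and a short amendment. Within the new list the largest possible imbalance in a stratum rises from 1 child to 3, hence from 2 to 6 per service with its two age strata. The primary model already includes service and age group, so the effect on the estimate is small. Therapists are fixed to one arm at about 8 children each, so some caseloads may shift slightly. The remedy removes nearly all certainty but lowers guessing only modestly.
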